## Abstract

**Background:**

It is essential for medical treatment that patients and medical staff can communicate about acute complaints, pre-existing conditions, and the treatment procedure. Misunderstandings can have far-reaching consequences, particularly in time-critical emergencies, which require rapid assessments and decision-making and in which interpreters are rarely available.

In this study, we aim to develop a digital communication tool that is to help paramedics communicate with patients who speak hardly any or no German, to monitor its implementation, and to investigate its effect on communication between foreign-language patients and staff. Furthermore, a large amount of data on patients that are cared for in emergency medical services in Germany are collected for the first time.

**Methods:**

To consider the complex situations of paramedic care and to meet paramedics’ demands, we use an action-oriented research approach to develop the tool. We include the staff of the participating emergency medical service stations and software designers in our approach. The tool is then used and evaluated within an open interventional, non-randomised study with two control groups. Control group 1 (German-speaking patients) and control group 2 (non-German-speaking patients treated without the tool) are recruited starting from the first study phase. In the second study phase, an intervention group is additionally recruited, i.e. non-German-speaking patients with whom the tool is used.

The primary outcome of the clinical trial is improved communication with non-German-speaking patients in emergencies by means of the communication tool. The secondary outcome is an improved quality and quantity of the collected information. We exploratively observe on-scene times, demands for emergency physicians, and the usage of the intervention. By recording patients’ clinical parameters, we consider the severity of the health restrictions.

**Discussion:**

Our study is an innovative research project in paramedic healthcare comprising the development of a digital communication tool to overcome language barriers in emergency medical services and investigating its usability, acceptance, and effect on communication, in short, its usefulness and value for paramedic care. Additonally, we expect to gain comprehensive information on rescue operations.

**Trial registration:**

German Clinical Trials Register, DRKS00016719, registered 08 February 2019, World Health Organization Trial Registration Data Set, http://apps.who.int/trialsearch/Trial2.aspx?TrialID=DRKS00016719

## Background

### Language barriers in the provision of paramedic care in Germany

Almost one-fourth of Germany’s population, 20.8 million inhabitants, have a migration background [1]; 10.6 million people have a foreign citizenship [2]. Additionally, 180,000 to 520,000 undocumented migrants lived in Germany in 2014 [3]. This number has presumably increased in recent years. No official data on the language skills of migrants in Germany are available [4]. Even though the majority probably speak German fluently, a substantial number is assumed to be unable to communicate sufficiently in German. This number of migrants living in Germany with no or little knowledge of German has probably increased in recent years because about 0.9 million asylum seekers and refugees came to Germany between 2015 to 2017 [5]. In addition to foreign residents, 37.5 million foreign tourists visit Germany per year (data for 2017) [6]. Germany is the most important destination for business trips in Europe [7], and is a transit country for travellers and long-distance transports. Moreover, 286,000 seasonal agricultural workers come to Germany every year (data for 2016) [8], many of them from Eastern Europe.

Some of these non- or barely German-speaking residents, tourists, business travellers, or migrant labourers may need medical emergency care during their stay in Germany. Communication about acute symptoms and pre-existing conditions is the basis of any medical treatment. In a representative study in 2006/2007 on the largest foreign nationality groups at that time (from Turkey, former Yugoslavia, Italy, Greece, and Poland), 10% of the respondents declared that they encountered difficulties in medical consultations due to insufficient language skills – even though the very large majority of these respondents had been living in Germany for more than 8 years, most for even more than 20 years [4, 9]. The German Government estimates that about 20% of all new immigrants will permanently need interpreter assistance when using health services [10]. Research has shown that refugees and asylum seekers in Germany experience difficulties when seeking health care, especially due to language barriers. This limits physician-patient communication [11–13]. Especially when no interpreters are available, situations of mutual incomprehension are a great challenge for patients who speak hardly any or no German and the medical staff who treat them.

In emergency care, the option of on-site interpretation is mostly very limited. Migrant and refugee patients in Germany are more likely than Germans to seek paramedic and out-of-hour medical care, however [14, 15]. Especially in out-of-hospital medical emergencies it is crucial for the paramedic staff to understand the current complaints of the patients, their characteristics and duration of acute symptoms as well as pre-existing conditions, allergies, or drug treatments. Communication difficulties can lead to inaccurate initial assessment and misdiagnosis, which may increase the risk of ensuing incorrect clinical decisions and treatment. This can have potentially life-threatening consequences for the patients. It might also cause unnecessary psychological stress to both patients and medical staff.

Some findings have indicated that the quality of care is inferior for patients with limited language proficiency: Language barriers delay transport to hospitals [16], even though in many emergencies, time is a crucial factor for the patient’s outcome. Language barriers may increase the likelihood of (unnecessary) intubation and intensive care during rescue missions with trauma patients [17]. Lee et al. [18] find that language barriers between emergency physicians and adult patients increase the probability of being admitted to hospital – probably partly as a precautionary measure.

Ignorance of the medical history of the patients and/or misinterpretation of symptoms may also lead to incorrect decisions regarding the choice of hospital. Especially in rural areas, paramedics often have to decide whether to take a patient to a small hospital that is close by and provides basic medical care (or choose between different small hospitals that provide different medical specialities such as obstetrics, chest pain units, or stroke units) or to take the road (and the time) to a hospital that offers maximum medical care.

Moreover, the recent Emergency Paramedics Act (Notfallsanitätergesetz, NotSanG) in Germany has given more competence and responsibility to the paramedic staff so that they can autonomously provide therapeutic measures. Understanding the patients’ situations has therefore become even more important for therapeutic decision-making in the field.

In summary, language barriers play an important role in paramedic care in Germany. Overcoming these barriers might be of high value for patients, health care providers, and the emergency medical system. Digital communication tools designed for the use in health care may help to improve communication in medical consultations [19]. The implementation of a tablet-based application software (app) for medical history taking in a German transit camp for refugees and asylum seekers has shown that this is accepted by most patients and can be implemented well [20, 21].

However, this app was developed for patients seeking primary care and who may enter their data themselves; the information is then translated for the general practitioner. Emergencies require a different content and a different approach: Completely different clinical pictures and diseases have to be considered. The handling must be done by the medical staff, resulting in different user interface and menu navigation. Paramedics may not only be required to gather information from the patients, but also to give them essential information. Additionally, time pressure in emergencies makes it challenging to develop a reliable, rapid-to-use application software: On average, on-set time of medical emergency missions before transportation to hospital is 16.9 min with and 22.3 min without accompanying emergency physician [22].

### Medical emergency care in Germany

Medical emergency care in Germany is typically organised and provided on the district level. It is either provided directly by the municipality or district (“kommunaler Rettungsdienst”), or it is contracted to non-profit organisations or private companies. Costs incurred by the rescue service are reimbursed by the health insurance.

There are regulations regarding qualifications of paramedic and medical staff and respective personnel on different types of emergency vehicles. Some of these regulations differ from state to state, but generally, paramedics provide the first level of emergency care; emergency physicians provide backup in life-threatening situations. The emergency physician is typically a physician with special training and a board certification in emergency medicine. There are currently two non-physician emergency professions: In 2015, the “Rettungsassistent”, requiring a 2-year theoretical and practical training, was replaced by the profession of “Notfallsanitäter”, a highly professional emergency care provider. This requires 3 years of training. A Notfallsanitäter has more responsibility because they may provide therapeutical measures without prior consultations of the emergency doctor, and they have more competencies to assist the emergency physician on scene on a high level. Paramedics are thus trained to respond to emergencies and can handle most rescue missions by themselves. Emergency physicians are only called out to seriously injured or critical patients to provide intense on-scene care and typically join the paramedic staff on the emergency scene (rendez-vous approach). Fewer than one-fifth (18%) of all the emergency operations in Germany include an on-site emergency physician, however [22].

Most recent data on emergency operations in Germany are from 2012/2013: approximately 12 million operations were carried out Germany-wide by public paramedic services. The deployment rate was 147 responses per 1000 inhabitants and year. However, only approximately half of these responses were emergency operations. The other half were ambulance transport services (transport of non-emergency patients, e.g. home from hospital). The time span until paramedics arrived on the scene averaged 8.4 min. Within 16.9 min, nearly all (95%) emergency sites were serviced [22].

### The aim of the study

In this study, we aim at developing, implementing, and evaluating a digital communication tool that helps paramedics to obtain (and give) essential information from (and to) non-German-speaking patients in their native language or in a language they are proficient in, and thus to overcome language barriers. We also wish to assess how the intervention affects the quality of information gathered from patients and how the paramedic staff perceives it. For this purpose, we conduct a clinical trial. We expect to gain comprehensive understanding of the possible benefits and constraints for the use of this tool in paramedic care. In addition, comprehensive information on healthcare encounters with non-German-speaking patients in emergency medical services is collected for the first time.

## Methods and study design

Different methodological approaches will be combined for the different study objectives of development, implementation, and evaluation. These are carried out in different time frames (cp. Fig. 1).

**Fig. 1 Fig1:**
[figure not shown]
Timeline of the study

First, the communication tool will be developed using an action-oriented research approach within the first 12 months of the project. Simultaneously, a clinical study will be prepared and data of two control groups will be recruited. Then, the developed app will be implemented into the emergency service procedures, and the phase of recruiting the intervention group begins. Finally, we will evaluate the obtained data. In the following, the methodological approaches are described in more detail.

### Action-oriented research approach for development and implementation

#### Data collection and data analysis

The communication tool will be developed and implemented using an action-oriented research approach. This implies that researchers will develop the intervention in close collaboration with actors in the field, in this case, the paramedic staff of four emergency medical service stations in central Germany (see below, study site and study setting). Paramedics will be involved in focus group discussions, informal background discussions, case conferences, and analyses of emergency cases with non-German-speaking patients. In addition, paramedics will perform extensive testing with beta versions in role-play test cases. Focus group discussions and testings with role plays with case trainings will be documented by the researchers by creating minutes and result logs. The suggestions by the paramedics for modification will be discussed and subsequently included in the development process. This is intended to be a circular process with several rounds of discussions and adjustments.

We will use these techniques to provide input for the communication tool in a first step, and to improve the content and user interface design of the app in a second step. An advantage of this approach is that it will enable us to consider perspectives from different stakeholders, to understand and take into account the needs of end users, and to respond flexibly to unexpected challenges that arise when the app is used in the field. We will also discuss and plan the implementation of the tool into the daily routine to anticipate potential obstacles in practice. This approach therefore ensures that the tool is ready to be used in the daily routine of the paramedics.

If no significant new requests for modification are reported, we will develop a first stable version of the app, which is to be tested with patients for a period of several weeks, accompanied by field observations and supported by technical backup. Suggestions for improvement and any necessary adjustments will be introduced in a final version, which will then remain unchanged during the clinical trial phase of intervention group recruiting.

Interpretation and processing of data in this project are oriented towards the goal of developing and implementing the communication tool. We therefore use the technique of identifying central statements as proposed by Ruddat [23] to create the tool requirement profile.

In addition, quantitative questionnaire surveys will be conducted shortly after the successful implementation and after 6 months to determine the usability and the subjectively perceived quality and attractiveness of the app. To assess the usability of the app, we will use the System Usability Scale (SUS) by Bangor et al. [24], and for its perceived quality and attractiveness we will use the AttrakDiff Questionnaire by Hassenzahl et al. [25]. Additionally, we will collect socio-demographic information on the paramedics such as age, gender, professional qualifications, and work experience. These factors may affect their willingness to use a digital tool and their perception of it. This two-stage survey enables us to assess whether and how the perception and acceptance of the tool change over time.

The questionnaires on the usability, quality, and attractivity of the app will be analysed mainly using descriptive statistics. Correlation analyses will be carried out aditionally to identify, for example, associations between the demographics of the paramedics and the responses they make to the questionnaires. We will thus use quantitative methods for analysing the questionnaire surveys, and a qualitative analysis to summarise focus group discussions and testings.

#### Recruitment of paramedic staff and informed consent

Before we start the action-oriented research phase and the first data-collection phase for the clinical trial, all paramedics of the four participating emergency medical service stations will be informed about the aims and process of the study. The paramedic staff are then invited to participate in focus group discussions and testing rounds with role plays in test cases. Inclusion criteria are thus met by all paramedics who are employed in one of the four rescue stations. They need to declare informed consent for participation and for documentation of the discussion processes and results. Paramedics have the right to withdraw from the study at any point, and any data containing personal information will be deleted immediately. However, minutes and result logs will not contain any personal data, and questionnaire data are also collected anonymously. This means that any given information cannot be deleted. We expect the complete paramedic staff (*n* = 131) to take part in the study. There are 23 paramedics in Wendhausen, 28 in Königslutter, 40 in Helmstedt, and 40 in Braunschweig. Focus group discussions are planned with 6–8 paramedics. Participation will change, so that ultimately a large part of the staff of each rescue station will have been involved in the development process. Moreover, we will ensure that female and male paramedics and paramedics with different professional experience are involved in the development process.

### Clinical trial

In order to evaluate the effect of the developed app, we will conduct a prospective open intervention study. The main purpose of the clinical trial is to assess how the use of the app affects the perceived quality of understanding of non-German-speaking patients from the paramedics’ point of view **(primary outcome)** and how it affects the quality and quantity of information obtained from patients with language barriers **(secondary outcome).** In addition, we will assess whether the tool is perceived as helpful and easy to handle in daily use by the paramedics.

For this purpose, two different patient control groups are recruited and compared with one interventional patient group. Control group 1 consists of German-speaking patients, whereas control group 2 consists of non-German-speaking patients with whom the communication tool is not used. The interventional group consists of non-German-speaking patients with whom paramedics use the tool to communicate with patients. German-speaking control group 1 serves as baseline for on-scene times, intubation rates, and requests for on-scene emergency doctor support. The recruitment period for this group will be at least 12 months because a very large total number of cases is necessary for the selection of matched control groups. By comparing data on control group 2 and on the interventional group, the immediate effect of the tool on communication and information gathering with non-German-speaking patients can be analysed.

As to the primary outcome, we expect that using the tool, paramedics perceive the communication with non-German-speaking patients as easier and more fruitful. Therefore, we will analyse paramedics’ feedback on questionnaires for each emergency drive with foreign-language patients concerning the communication and mutual understanding with patients (see below). Paramedics are asked to report their experience with the tool to assess its acceptance and usability (see above).

Moreover, this study attempts to generate first knowledge about the extent and relevance of language barriers in emergency operations. With regard to the secondary outcome (quality and quantity of information obtained from the patient), we will be able to compare non-German-speaking patients with German-speaking patients and take demographic and medical aspects into account.

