#### Inclusion criteria for patients

Patients who meet the following criteria are eligible to participate in the study:
Control group 1: German-speaking patients of all ages who do not use the app.Control group 2: Non-German-speaking patients of all ages who do not use the app (i.e. within the first period of recruitment and because of drop-out in the second recruitment stage)Interventional group: Non-German-speaking patients of all ages who speak one of the available languages (cp. Table 2) and who are responsive to use the app.

**Table 2 Tab2:** Supported languages

• Arabic: possible dialects are Syrian Arabic, Egyptian Arabic, Moroccan Arabic (spelling Modern Standard Arabic) • Bosnian • Croatian • Czech • Dari • English • French	• Italian • Kurdish: possible dialects are Sorani and Kurmanji • Lithuanian • Pashto • Persian • Polish • Russian • Serbian • Turkish

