#### Drop-out criteria for patients from the interventional group

When the intervention takes place, paramedics can refuse to use the app at any time. They are not to use the app when it presumably places the patient or themselves at risk (e.g. rescue operation on a busy and unblocked motorway). Furthermore, the app is not to be used in emergencies with immediate action implications (e.g. cardiopulmonary resuscitation or transport to the hospital necessary without any delay) or if the patient has a severe limitation of consciousness. If patients do not speak languages provided in the app (cp. Table 2), they are excluded from the interventional group but serve as control patients in group 2. Patients who meet the eligibility criteria but with whom paramedics do not use the intervention will be analysed separately.

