#### Data analysis of the clinical trial

Characteristics of intervention and the two control groups are analysed using descriptive statistics regarding their demografics, medical conditions, assessed communication and native languages (where applicable), and aspects of the emergency operation. Differences between patients of the intervention group and the control groups will be tested for statistical significance using Chi-squared or Mann-Whitney *U*-Tests where applicable. In addition, the groups will be compared according to the recruitment centres in which patients were recruited. Relations between medical aspects of the emergency operation or demographic aspects and the assessed mutual understanding will be analysed using correlation analyses. Changes between control group 2 and the intervention group as to the perceived quality of understanding and to the quantity and quality of obtained information of patients will be analysed using paramedics’ feedback on questionnaires and comparing the content of the free text fields in the DIVI-protocols. In order to enable a comparison between non-German-speaking and German-speaking patients, a control group matched by age, sex, medical condition, and emergency situation will be drawn from the very large group of the German-speaking patients. Then, for example, on-scene times, rates of intubations, and requests for on-scene emergency doctor support can be compared.

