#### Integration of the communication tool into the rescue chain

When the notification of the emergency call indicates language barriers, paramedics may preselect the mode (adult or child), patient’s sex, and mother language on their way to the emergency site. On-scene, paramedics can perform a rapid assessment of patients’ complaints and pre-existing conditions – also with third parties – in order to decide which actions to take, e.g. whether an emergency doctor should be called to the scene, to which hospital the patient should be taken, and with which symptoms or suspected diagnosis the hospital should be notified. Paramedics may document the patient’s answers to the questions posed in the app. They may also explain therapeutic measures. A more detailed medical history can be taken during transport. This additional assessment may contain information on medication or known allergies and other information that might not be directly relevant for paramedic emergency treatment and transport but might be of interest for further treatment in the hospital. The app generates a report in German, which also serves as a documentation of the communication process. If possible, information can be shared with the hospital before or directly after arrival (cp. Fig. 3).

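### App use that begins after arrival defines the intervention group, so app missions tend to show longer on-scene times even if the app has no effect; the size depends on when use starts

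*Protocol article*

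**What the plan says.** All references are to the protocol article.

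- **Group formation.** Under Clinical trial: "The interventional group consists of non-German-speaking patients with whom paramedics use the tool to communicate with patients". The entry under Inclusion criteria for patients is worded by ability rather than use: "Non-German-speaking patients of all ages who speak one of the available languages (cp. Table 2) and who are responsive to use the app".
- **Comparators.** Control group 2 is non-German-speaking patients "who do not use the app (i.e. within the first period of recruitment and because of drop-out in the second recruitment stage". The Clinical trial section reads its contrast with the intervention group as the tool's immediate effect on communication and information gathering. For German-speaking patients: "German-speaking control group 1 serves as baseline for on-scene times, intubation rates, and requests for on-scene emergency doctor support".
- **Non-users in phase 2.** Under Drop-out criteria, crews may decline the app at any time, and it is not used in urgent situations ("e.g. cardiopulmonary resuscitation or transport to the hospital necessary without any delay") or when consciousness is severely limited. The section ends: "Patients who meet the eligibility criteria but with whom paramedics do not use the intervention will be analysed separately".
- **Analysis.** Data analysis of the clinical trial describes the groups, including aspects of the operation, and tests differences by Chi-squared or Mann-Whitney tests. It then describes a German-speaking control group matched on age, sex, condition and situation: "Then, for example, on-scene times, rates of intubations, and requests for on-scene emergency doctor support can be compared". No stated rule uses the app's start time.
- **Status and workflow.** The Abstract lists on-scene time as exploratory. Under Integration of the communication tool into the rescue chain, mode, sex and language may be preset en route, and "A more detailed medical history can be taken during transport".

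**The concern.** Exposure is acquired during the interval that is also an outcome. A crew that leaves after a few minutes has had less opportunity to start the app than one that stays half an hour. The app group therefore loses some short missions, while phase 1 control missions enter at any length. The minutes before the app was opened are also counted as app time. This is a form of immortal-time bias. It arises even with identical case mix, so matching on age, sex, condition and situation does not remove it, and neither does a rank test.

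The Background reports that language barriers delay transport and that time is critical in many emergencies. Readers will therefore look to on-scene time to see whether the tool costs minutes, and part of any apparent delay could come from how the groups are formed. A weaker version applies to the quantity of recorded information, since longer contact may yield more of it.

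**Working it through.** The plan gives no figure for this bias, so there is none to reproduce. The check asks how large the difference is when the app does nothing.

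**Inputs from the document.** Mean on-scene time is 16.9 min with and 22.3 min without an emergency physician (Background). The 16.9 also appears there as the time within which 95% of sites were reached, so that mean is itself uncertain.

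**Assumptions (not in the document).**
- On-scene time S is log-normal with CV 0.4 to 0.6.
- On-scene app start U is log-normal, independent of S, with median 3, 6 or 10 min and log-SD 0.7.
- A mission is an app mission if U < S.

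**Formula.** Let m be the mean of S, σ² = ln(1 + CV²), μ = ln m − σ²/2 and s = √(σ² + 0.7²). Put a = (μ − ln median)/s and b = (μ + σ² − ln median)/s. The share of app missions is Φ(a), and their excess over all-comers is m × [Φ(b)/Φ(a) − 1].

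**Worked case** (m = 22.3, CV 0.5, median start 6):
- σ² = ln 1.25 = 0.2231; μ = 2.9930; s = 0.8445.
- a = (2.9930 − 1.7918)/0.8445 = 1.422, so Φ(a) = 0.9226.
- b = (3.2161 − 1.7918)/0.8445 = 1.687, so Φ(b) = 0.9542.
- Excess = 22.3 × (0.9542/0.9226 − 1) = 0.76 min. Simulation gives the same value.

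**Range over both means and CV 0.4 to 0.6:**

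| Median start | App missions | Spurious excess over all-comers | App users starting after minute 5 |
|---|---|---|---|
| 3 min | 96–99% | 0.07–0.38 min | 21–23% |
| 6 min | 84–94% | 0.46–1.42 min | 53–58% |
| 10 min | 66–82% | 1.22–2.95 min | 76–80% |

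**Other start distributions.** The combined mean is 0.18 × 16.9 + 0.82 × 22.3 = 21.3 min, using the 18% physician share in the Background. With this mean and SD 8 to 12 min:
- A fixed start at 5 min gives 0.0 to 0.1 min.
- Exponential starts with mean 10 min give 0.8 to 1.7 min. The Mann-Whitney test then rejects in 10–17% of trials at 75 per group, against a nominal 5%.
- Exponential starts with mean 20 min give 1.5 to 3.1 min.

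**Recorded information.** The shift in SD units is r × excess/SD of S. In the worst case above (m = 16.9, CV 0.6, median 10) with an assumed r = 0.3, it is 0.3 × 2.95/10.14 = 0.09 SD.

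**Placement of phase 2 non-users.** Inclusion criteria puts phase 2 drop-outs in control group 2; Drop-out criteria has eligible non-users analysed separately. If non-users arise only from short missions and are pooled with an equal-sized phase 1, the median-10 excess becomes 2.1 to 4.4 min. If they are set aside, it stays at 1.2 to 3.0. Neither reading removes the bias, because the app group still contains users only.

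**The case against.** Five points carry weight.

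1. A reader might infer that a mission can become an app mission only if the scene time is long enough. The document does not support that: the tool can be preset en route, first use on scene is meant to be rapid, and a fuller history can be taken in transport. A short scene time can therefore still go with app use. Presetting selects mode, sex and language, but questioning begins only with the patient, so the tendency remains in weaker form.
2. That workflow suggests early starts. At a 3-minute median the excess is below the one-minute resolution of the recorded times. This stands; the document states no start time, so neither the favourable nor the unfavourable case can be assumed.
3. On-scene time is exploratory, its named comparison is with matched German-speaking patients, and model choice for exploratory outcomes may sit in an analysis plan not shown. This limits the importance. The group definition, however, is fixed in the protocol, and the start time must be kept at data collection.
4. Comparing app missions with phase 2 missions in which the app was never started gives roughly 5 to 13 min under the same model. That should not be read as the trial's bias: it assumes a comparator made up only of missions that were too short, whereas the document lists several other reasons for non-use and control group 2 also contains phase 1 patients.
5. Selection by urgency, consciousness and crew discretion is better documented than selection by duration. This is correct. Its net direction is unknown, since on-scene times for resuscitations and unconscious patients are not given.

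**Conclusion.** The point holds as a tendency of conditional size. Under no app effect, app missions tend to have longer on-scene times than control missions, by about 0.1–0.4, 0.5–1.4 or 1.2–3.0 min for median on-scene starts of 3, 6 or 10 min. These figures rest on assumed start times, spread and independence of start from mission length. They are negligible if crews start early and smaller if use often begins in transport.

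A reader might infer that the secondary outcome is seriously inflated or that the primary outcome is biased by this route. Neither is supported: the information shift is at most about 0.09 SD on an assumed correlation, and nothing here concerns perceived understanding. The reason to act is that a spurious delay of one to three minutes could be held against a harmless tool, and the correction may become impossible once the linking number is deleted.

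**What to change.** 1. **Data.** Keep one absolute clock time per session for the first question played to the patient, not for presetting en route. Link it to the mission before the operational number is deleted. The protocol mentions time-to-click intervals, which may not include a clock time.
2. **Main on-scene analysis.** Analyse time from arrival at patient to departure from the scene (both in Table 1) with app use as a time-dependent exposure, for example in a Cox model. Missions are unexposed until the first question, controls are unexposed throughout, and missions where use begins only in transport count as unexposed on scene. In the null model above, started and not-yet-started missions still on scene have the same departure rate, so the rate ratio is 1.00.
3. **Landmark as sensitivity analysis only.** A 5-minute landmark would count 53–80% of users as unexposed for median starts of 6 to 10 min. Report how many users start after it.
4. **Eligibility-based comparison.** Compare all phase 2 missions that meet the eligibility criteria, whether or not the app was used, with phase 1 missions that meet the same criteria as far as recorded data allow. This addresses selection by urgency, consciousness and discretion, which the time-dependent model does not.
5. **Reconcile** Inclusion criteria and Drop-out criteria on where phase 2 non-users belong.

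The cost is one field in the device log and a few sentences of analysis text. The drawbacks are that late users contribute unexposed time up to their start, times are rounded to the minute, and the eligibility comparison dilutes any effect of actual use.
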